# Abstract of protocol

| Study title | Registration study on treatment outcome of Chinese acute ischemic cerebral stroke |
| --- | --- |
| **Sponsor** | Guangdong Techpool Pharmaceutical Stock Co., Ltd |
| **Principal Investigator** | [name], Peking University First Hospital |
| **Study staging** | Non-interventional case registration study |
| **Planned number of study sites and patients** | 10,000 cases |
| **Study schedule** | From March 2015 to March 2017, the expected inclusion time is 18 months |
| Study Background Overview | The stroke is one of the diseases seriously threatening people's health, and has the features of high incidence, high morbidity and high recurrence rate, among which the acute ischemic stroke accounts for about 70% to 80%. The patients will not only experience physical dysfunction, but disorders in mental state, social function and other aspects, which would seriously affect their quality of life, and bring a heavy burden on their families and the society. Therefore, the scientific and rational prevention and proper treatment of stroke is very important.  After the tireless research by scientists and clinical experts, a lot of achievements have been obtained for the prevention and treatment of AIS over the past decade. And in the whole world, there is still no adequately effective drugs or methods for the treatment of AIS, except for the ultra-early thrombolytic treatement and antiplatelet therapy with aspirin.  In China, the situation of the drugs for ALS is particularly complex, and, according to the relevant reports, there are more than 100 types of drugs for the clinical treatment of AIS. There was no data from clinical investigations of large sample size, to guide how to achieve good therapeutic effect, or possess a better cost - effectiveness through the combinations of different types of drugs. |
| Study objective: | Primary study objective:  Analysis of current treatment situation in acute phase of acute ischemic stroke in real-world settings。  Secondary study objectives  (1) Comparison of effects of various drug combinations in treatment of acute ischemic stroke in real-world settings.  (2) Analysis of cost-utility of various drug combinations in treatment of acute ischemic stroke.  (3) Analysis of occurrences of complications and adverse events during treatment in hospital in patients with acute ischemic stroke.  (4) Analysis of effects of TOAST typing on specific therapy regimens in acute phase of acute ischemic stroke. |
| Study design | This was a registered, prospective, multi-center clinical study. The study was planned to included 10, 000 patients with acute ischemic stroke (AIS) and record treatment regimens, treatment outcomes and medical expenses during hospitalization in real clinical practice. This study was to collect patients' data through a electronic data capture system (EDC).  According to the recommendations for treatment and follow-up observations in acute phase in the "Guidelines on diagnosis and treatment of acute ischemic stroke in China 2014 (Draft)", the patients with stroke were planed to receive 5 visits, which occurred at admission (baseline assessment, visit 1), 7 days ± 2 days after medication (visit 2), at discharge (visit 3), 90 days ± 14 days after medication (visit 4, outpatient service or telephone follow-up), and 360 days ± 28 days after medication (visits 5, telephone follow-up), respectively.  In the baseline phase, the investigators should verify the inclusion/exclusion criteria, obtain the patients' informed consent, and try to collect the demographic information, past history, onset and admission conditions, and vital signs of the patients; and collect the following data of clinical examination: ECG, laboratory tests (blood routine, blood glucose, blood lipids, hepatic and renal functions, cardiac enzymes, serum electrolytes, coagulation) and imaging findings, and assess Glasgow Coma Scale, NIHSS score, mRS score and EQ-5D Scale. Seven days ± 2 days after medication, the vital signs of the patients were recorded and the NIHSS scores were accessed again. At discharge, the treatment regimen, vital signs, ECG and above laboratory tests results were recorded during hospitalization, and the Glasgow Coma Scale, NIHSS score, mRS score and EQ-5D scale were accessed, and the medical expenses during hospitalization was also collected. On 90 ± 14 days after medication, the recurrence of stroke, survival conditions and re-admissions were collected; the medical expense until this visits since discharge was recorded; and the mRS score, EQ-5D scale and MMSE scale (only applicable for the patients visiting the hospital) were accessed. On 360 days ± 28 days after medication, another telephone follow-up was given again, to ask the patient's health status, access mRS score, EQ-5D scale, and collect medical expenses.  Only the drug combinations during hospitalization and the occurrences of adverse events during the study period were recorded.  If the patient was discharged on 7 ± 2 days after medication, it should be handled as a discharge note at this time. |
| **Inclusion criteria** | 1. Age≥18 years 2. In conformity with the diagnosis criteria (draft) of China 2014 Guidelines for Diagnosis and Treatment of Ischemic Cerebral Stroke 3. The onset time of thrombolytic patients are within the time window of thrombolysis 4. The onset time of thrombolytic patients are within one week 5. The patients or legal guardians can understand and sign the informed consent form |
| **Exclusion criteria:** | 1. Cranial CT/MRI can display the presence of cerebral hemorrhage 2. The expected survival time of patients less than three months because of complicated serious systemic diseases i 3. the patients cannot provide continuous follow-up information by investigator judgments |
| **Primary efficacy endpoint** | The proportion of patients with good prognosis (mRS=0-2 points) at 90 days after treatment |
| **Secondary efficacy endpoint** | 1. The proportion of patients with poor prognosis (mRS= 3-5 points) and death (mRS=60 points) at 90 days after treatment 2. The changes in National Institutes of Health Stroke Scale (NIHSS) at discharge from baseline 3. The changes in EQ 5 visual analogue scale (EQ-5D, VAS) at discharge from baseline |
| **Safety parameters** | 1. Incidence rate of symptomatic intracranial hemorrhage transformation during the hospital stay 2. Adverse events 3. Vital Signs 4. Laboratory tests (blood routine test, blood glucose, blood lipids, liver and renal functions, myocardial enzymes, serum electrolytes, and coagulation function) 5. ECG examination |
| **Exploratory analysis** | Analysis on the prescriptions of acute specific treatment for different TOAST types  Stroke recurrence rate and incidence rate of post-stroke dementia at 90 days after treatment |
| **Pharmacoeconomic evaluation** | Calculate the cost/utility of the protocol of combinations of different drugs, and ascertain the optimal protocol of hospital treatment of patients with acute cerebral stroke.  As for the costs, only the direct cost is collected, and the indirect cost and implicit cost are not collected. The quality adjusted life years (QALYs) is adopted for the utility analysis as the health outcome parameter. |
| **Statistical methods** | A descriptive statistical analysis is made on the proportion of patients with good prognosis (mRS=0-2 points) and the proportion of patients with poor prognosis (mRS=3-5 points) and death (mRS=6 points) at 90 days after treatment, the corresponding number of cases and the proportion are calculated, and χ^2^ or Fisher's exact test is adopted to compare the inter-group difference. If the inter-group difference is of statistical significance, the Bonferroni method is adopted to adjust the size of test α value, and inter-group pairwise comparison is further made.  The changes in National Institutes of Health Stroke Scale (NIHSS) and EQ 5 visual analogue scale (EQ-5D) at discharge from baseline: if the score difference between before treatment and after treatment is in normal distribution and satisfied homoscedasticity, then analysis of variance is performed. If the statistical test results of the analysis of variance are of statistical significance, statistical analysis is further performed, and the Bonferroni test is carried out for pairwise comparison. Otherwise, the Kruskal Wallis method is adopted to perform statistical test. If the statistical test results of the Kruskal Wallis are of statistical significance, statistical analysis is further performed, and the Wilcoxon rank test is carried out, and the Bonferroni method is adopted to correct P value for pairwise comparison.  The descriptive statistical method is adopted to perform the analysis on all the data. As for the measurement data, number of cases (missing number), mean value, median, standard deviation, first quartile, third quartile, maximum and minimum are described, and the 95% confidence interval of the mean is calculated; as for the enumeration data, the frequency is described. It the hypothesis test needs to be carried out, the corresponding hypothesis test methods are adopted according to the nature of materials and the purpose of the test.  Unless otherwise specified, the hypothesis test adopted by this study is two-sided test with 0.05 as the size of test. P value ≤ 0.05 meant that the difference is of statistical significance.  Based on whether the score difference before and after treatment is in normal distribution, the paired t-test is adopted to make an inter-group comparison on measurement data, or the Wilcoxon signed rank test is used for analysis; χ ^2^ test or Fisher exact probability test is adopted to analyze the enumeration data; the Wilcoxon rank test is adopted to analyze the ranked data. |

#

# Study flow diagram

| **Phase** | **Baseline phase** | **Treatment phase** | | **Follow-up period** | |
| --- | --- | --- | --- | --- | --- |
| Visit | V1 | V2[a](#bookmark) | V3 | V4  (Outpatient or  telephone visit) | V5  (telephone visit) |
| Days | At admission  Day 0 | 7 ± 2 days after administration | At discharge | 90±14 days after administration | 360±28 days after administration |
| Signing informed consent forms | × |  |  |  |  |
| Inclusion / exclusion criteria | × |  |  |  |  |
| Demographic materials and medical insurance type | × |  |  |  |  |
| Visit delay and visits accepted by emergency | × |  |  |  |  |
| Past medical history and risk factors^b^ | × |  |  |  |  |
| Onset and admission^d^ | × |  |  |  |  |
| Glasgow coma score | × |  | × |  |  |
| NIHSS score | × | × | × |  |  |
| mRS score | × |  | × | × | × |
| EQ-5D scale | × |  | × | × | × |
| MMSE scale ^e^ |  |  |  | × |  |
| TOAST classification |  |  | × |  |  |
| Vital Signs^f^ | × | × | × |  |  |
| ECG examination | × |  | × |  |  |
| Laboratory examination^g^ | × |  | × |  |  |
| Imaging examination | × |  |  |  |  |
| Treatment regimen^h^ |  |  | × |  |  |
| Combined medications | × | × | × |  |  |
| Adverse events^i^  Special attention should be paid to the symptomatic intracranial hemorrhagic transformation | At any time | | | | |
| Medical expenses^j^ |  |  | × | × | × |
| Recurrence, survival status and re-admission |  |  |  | × | × |

Note:

1. At visit 2, if the patient is discharged, please directly perform the evaluation related with visit 3.
2. The visit delay, visits accepted by emergency and AIS risk factors are the items that can be evaluated.
3. Past medical history includes: stroke, hypertension, diabetes, dyslipidemia, coronary heart disease, atrial fibrillation, carotid plaques, and history of tumor.
4. Onset and conditions at admission: stroke occurrence time, and main symptoms
5. MMSE scale is only applicable to the patients that receive follow-up visits at 90±14 days after the initiation of administration.
6. The vital signs include body temperature, pulse, respiration and blood pressure. The changes in body temperature 1 day and 24 hours after the onset need to be collected at visit 1.
7. Laboratory tests include: blood routine test, blood glucose, blood lipids, liver and renal functions, myocardial enzymes, serum electrolytes, and coagulation function.
8. The therapeutic regimen refers to AIS specific treatment, and the non-specific treatment needs to be recorded in the combined medication page.
9. The collection of adverse events starts from the signing of informed consent form to 30 days after the initiation of the last administration.
10. The medical expenses refer to the direct costs, including the direct medical costs and and direct non-medical costs. At discharge visit, the direct medical costs are acquired through the expense detailed list when the patient is discharged, and the direct non-medical costs (including the transportation expense, nutrition expense and family accompany expenses) are acquired through the inquiry of the patient or his/her family.

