**2 Study objective**

Primary study objective:

Analysis of current treatment situation in acute phase of acute ischemic stroke in real-world settings。

Secondary study objectives

(1) Comparison of effects of various drug combinations in treatment of acute ischemic stroke in real-world settings.

(2) Analysis of cost-utility of various drug combinations in treatment of acute ischemic stroke.

(3) Analysis of occurrences of complications and adverse events during treatment in hospital in patients with acute ischemic stroke.

(4) Analysis of effects of TOAST typing on specific therapy regimens in acute phase of acute ischemic stroke.

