Only the drug combinations during hospitalization and the occurrences of adverse events during the study period were recorded.

If the patient was discharged on 7 ± 2 days after medication, it should be handled as a discharge note at this time.

As the database can last for several years, whenever there is a need to supplement or modify the data, a retrospective modification / amendment can be carried out at any time. According to the inclusion, data tendency and management factors, it is possible that the duration may be longer; therefore, the patients who are preliminarily included and added during the late stage may be followed up after 3 months.

Techpool can terminate this study at any time due to any reason. The physicians participating in the disease registration study is responsible for notifying IRBs and/or ECs about the premature termination of the study.

If necessary, the disease evaluation can be evaluated more frequently. In this study, any valuable information collected at follow-up visit is recorded.

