# 5 Treatment regimen

In the study, the doctors can select the specific treatment regimen for cerebral stroke according to the patient's clinical medical history and characteristics of symptoms as well as the China 2011 Guidelines for Diagnosis and Treatment of Ischemic Cerebral Stroke. This study has no limitations on the selection, dose and treatment course of the treatment drugs.

According toChinese Guideline for Diagnosis and Management of Acute Ischemic Stroke2010, The specific treatment on acute ischemic cerebral stroke refers to the intervention with a certain link in the pathophysiological mechanism of ischemic injuries. Examples are given to the following common drugs for illustration:

1. Intravenous thrombolysis drug: rt-PA and urokinase.
2. Anti-platelet drugs: aspirin and Clopidogrel
3. Anticoagulants: including unfractionated heparin, low molecular heparin, ateroid, oral decoagulants and thrombin inhibitor.
4. Volume expansion drug: hydroxyethyl starch, and low molecular dextran.
5. Nerve protective agents: Edaravone, nicholin and ganglioside.
6. Cerebral blood flow perfusion improving drugs: butylphthalide, human urine kininogenase (Urinary Kallidinogenase for Injection).
7. Chinese herbal medicines: Shuxuetong injection, and Danhong injection.

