**Visit 3 (At discharge)**

- Vital Signs (Body temperature, pulse, respiration and blood pressure)
- Glasgow coma score
- TOAST classification
- NIHSS score
- mRS score
- EQ-5D scale
- ECG examination
- Laboratory tests (blood routine, blood glucose, blood lipids, hepatic and renal functions, cardiac enzymes, serum electrolytes, coagulation)
- Therapeutic regimen (namely the specific treatment of acute ischemic cerebral stroke)

The name (generic name), dose, administration method, initial medication time and medication duration of the treatment drug need to be recorded.

- Collect medical expenses

The direct medical costs are acquired through the expense detailed list when the patient is discharged, and the direct non-medical costs (including the transportation expense, nutrition expense and family accompany expenses) are acquired through the inquiry of the patient or his/her family.

The contents of the collected direct medical costs include:

1. Total inpatient expenses (including the self-paid part)
2. Category of comprehensive medical service: including general medical service expense, general treatment and procedure expense, nursing expense and other expenses
3. Category of diagnosis: including pathological diagnosis expense, laboratory diagnosis expense, imaging diagnosis expense, and clinical diagnosis expense
4. Category of treatment: including expense of non-surgical item and surgical treatment expense
5. Rehabilitation expense
6. TCM therapy expense
7. Western medicine expense
8. Category of Chinese medicines: including expense of prepared Chinese medicine and expense of Chinese herbal medicine
9. Category of blood and blood products: including expense of blood, expense of protein-like products, expense of globulin-like products, expense of blood coagulation factor like products, and expense of cytokine like products.
10. Category of consumables: including the expense of disposable medical materials for examination, the expense of disposable materials for treatment, and the expense of disposable materials for surgery
11. Other expense

- Concomitant treatment

The non-specific treatment drugs for acute cerebral infarction (dehydrants, antihypertensive drugs, antihyperlipemic drugs, hypoglycemic drugs, and anti-infective drugs etc.), supporting therapy, and drugs for the treatment of accompanying diseases.

- Adverse events

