**11.2 Reporting procedures**

**Adverse Events Reporting regulations:**

Time limit: within 24 hours

In the clinical study (from the time of signed ICF through 30 days after last dose of study medication), the subject should be given of appropriate therapeutic measures in case of any adverse event, no matter what kind of treatment received. The investigators or the authorized personnel must report them to the food and drug supervisory departments of the corresponding provinces, autonomous regions and municipalities directly under the Central Government within the time limit specified by the regulations based on the Adverse Drug Reaction Reporting and Monitoring Management Methods (WSBL No. 81) in case that the investigators judge that this event is not anticipatory. In accordance with the sponsor's SOP "Pharmacovigilance Policy", for the adverse events in the patients using the registered drug from the sponsor (Guangdong Techpool Pharmaceutical Stock Co., Ltd), the investigators should fill in Guangdong Techpool "Adverse Drug Event Report form", and submit the report form in written form to Guangdong Techpool within 24 hours after awareness:

| Guangdong Techpool Pharmaceutical Stock Co., Ltd. - Pharmacovigilance contact mode | |
| --- | --- |
| Hoteline | [contact] |
| E-mail | [contact] |
| Address | [name] |
| Post code | 200012 |

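### The adverse event collection period is stated in conflicting ways, two of them tied to the last dose, so descriptive adverse event percentages by regimen could partly reflect observation time

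*Protocol*

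**What the plan says.** The protocol words the adverse event period in several places:

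- **Study flow diagram, note 9:** collection runs "from the signing of informed consent form to 30 days after the initiation of the last administration". The note is attached to the adverse event row, which reads "Special attention should be paid to the symptomatic intracranial hemorrhagic transformation | At any time" and spans Visits 1 to 5.
- **Section 11.2:** both the adverse event and the serious adverse event rules run "from the time of signed ICF through 30 days after last dose of study medication".
- **Section 3, repeated in the Abstract of protocol:** "Only the drug combinations during hospitalization and the occurrences of adverse events during the study period were recorded". The study period is given no end date. The last scheduled contact is Visit 5, at 360 ± 28 days.
- **Sections 7.1 to 7.3:** adverse events are a listed procedure at Visits 1, 2 and 3. They are not listed at Visit 4 or Visit 5.
- **Section 2, secondary objective 3:** "Analysis of occurrences of complications and adverse events during treatment in hospital in patients with acute ischemic stroke".

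On exposure, section 5 states: "This study has no limitations on the selection, dose and treatment course of the treatment drugs". Its list of specific treatments includes "Anti-platelet drugs: aspirin and Clopidogrel" and oral anticoagulants. Drug timing is captured once, at discharge (section 7.2, Visit 3), when the "initial medication time and medication duration of the treatment drug need to be recorded". Visits 4 and 5 have no drug item.

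**The concern.** There are two linked problems.

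First, a site cannot tell from the protocol when to stop collecting adverse events. Note 9, section 11.2 and section 3 imply different stopping dates, and the visit lists suggest that nobody asks after discharge. A later analysis plan can choose an analysis window, but it cannot recover events that some sites had already stopped recording.

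Second, two of the wordings end the period by reference to the last administration or dose. In a registry with unrestricted treatment, that makes observation time a function of the regimen, which is the grouping whose effects the study sets out to compare. Adverse events are a named safety parameter (section 8.2) and the subject of secondary objective 3. A plain percentage of patients with an event, tabulated by regimen, would then mix safety with length of observation.

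**Working it through.** The protocol gives no adverse event rate, so there is no figure of its own to reproduce. The check has two parts.

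**1. The wordings applied to one patient.** Assume treatment starts on day 0, a single 14-day course is given, and discharge is on day 14. The course length and discharge day are assumptions.

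| Source | End of adverse event collection |
|---|---|
| Sections 7.1 to 7.3 (last visit listing adverse events) | Visit 3, day 14 |
| Note 9, if initiation means the start of that course | day 0 + 30 = day 30 |
| Section 11.2 (last dose) | day 14 + 30 = day 44 |
| Section 3 (study period, taken to Visit 5) | day 360 ± 28 |

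One patient therefore has four possible stopping dates, from 14 days to about a year. Note 9 and section 11.2 coincide only if initiation of the last administration is read as the last dose.

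**2. The dose-anchored wording applied to two course lengths.** Under section 11.2, the end of the window is the course length plus 30 days:

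- 14-day course: 14 + 30 = 44 days
- drug continued to day 360: 360 + 30 = 390 days

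The second course illustrates a drug taken long after discharge. Its end date could not be derived from the study data, because drug use is recorded only in hospital.

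Assume the same constant hazard under both regimens and a 30-day risk p of 5%, 10% or 20%. These values are assumptions. The daily hazard is h = −ln(1 − p)/30. The expected proportion with an event by day t is 1 − exp(−h·t), which equals 1 − (1 − p)^(t/30).

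| Assumed 30-day risk | 44 days | 390 days |
|---|---|---|
| 5% | 1 − 0.95^(44/30) = 7.2% | 1 − 0.95^13 = 48.7% |
| 10% | 1 − 0.90^(44/30) = 14.3% | 1 − 0.90^13 = 74.6% |
| 20% | 1 − 0.80^(44/30) = 27.9% | 1 − 0.80^13 = 94.5% |

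By construction the regimens are equally safe, so the whole difference comes from the length of the window. With one fixed window, such as 30 days, both regimens show the same 5%, 10% or 20%.

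**The case against.** The strongest reply is that the conflict is mostly loose wording.

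- Note 9 is the only explicit collection rule. The flow diagram row is footnoted to it, so the row sets no separate end date. Section 11.2 is a reporting rule that nearly matches note 9, and the gap between the two may come from translation. Objective 3 defines what is analysed, not when collection stops. This stands in part: it is wrong to count the row and the objective as further collection windows. It does not remove the conflict between note 9, section 11.2, section 3 and the visit lists.
- The last administration could be read as the last recorded in-hospital dose, whose date follows from the start time and duration entered at discharge. That reading is possible, and no section says that listed drugs continue after discharge. But the protocol does not adopt it. With course length unrestricted and antiplatelets and oral anticoagulants on the list, continuation is a reasonable inference.
- Safety analysis is mainly descriptive (section 10.4). The only between-group safety test named is for symptomatic intracranial haemorrhage, which section 8.2 confines to the hospital stay. This stands, and it limits the consequence to descriptive tables.
- Both example combinations in the Brief introduction contain an antiplatelet drug, so for that pair an antiplatelet continued after discharge would lengthen both windows. This also stands: the size of any imbalance between actual regimens is unknown.
- The long window needs events to be ascertained after discharge, and the Visit 4 and 5 lists do not provide for that. This is correct. It makes the illustration an upper-end case, and it is itself part of the contradiction.

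**Conclusion.** The protocol contradicts itself on how long adverse events are collected, and that rests on its text alone. The effect on comparisons between regimens is conditional. It arises if a dose-anchored wording is applied, if listed drugs continue after discharge to a different extent across regimens, and if crude percentages are tabulated by regimen. For patients who do continue a listed drug, the end of a dose-anchored window cannot be derived from the data collected.

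The range of 7.2% to 27.9% over 44 days against 48.7% to 94.5% over 390 days illustrates direction and possible scale. It rests on an assumed 30-day risk, a hazard held constant for more than a year after acute stroke, and assumed course lengths. It is not an estimate for this registry.

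A reader might infer that adverse event incidence in this study is not comparable between regimens at all, or that the last-dose date is missing for every patient. The documents do not support either reading. The symptomatic intracranial haemorrhage endpoint has its own window. A study-period rule would give all completers the same nominal follow-up. For courses completed in hospital, the end date can be worked out from what is recorded. The point is worth correcting because the contradiction is certain and the remedy is cheap.

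**What to change.** 1. Reconcile the Study flow diagram (adverse event row and note 9), section 3 with the matching text in the Abstract of protocol, sections 7.1 to 7.3 and section 11.2 to one collection period. Its end should be defined and should not depend on the regimen. The choice of period is for the sponsor and investigators.
2. Make the visit lists match it. If the period extends past discharge, adverse events must appear at the later visits it covers. If it does not, the flow diagram row should stop accordingly. Define study medication or remove the term.
3. Tabulate adverse events by regimen over a fixed number of days from consent or admission, within the agreed period.
4. Report in-hospital events for objective 3 with patient-days as denominator. Admission to discharge is not the same length for every patient, so a plain percentage would carry a milder form of the same problem. A rate per patient-day corrects for this only in so far as the hazard is roughly constant, so it complements the fixed-day table.

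The cost is a change of wording and tabulation, plus an adverse event item at later visits if the period reaches them. Events outside the common window are listed separately and do not enter the comparison. Events that sites have already stopped collecting cannot be recovered.
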